### Study population

2.2

The study will identify informed and written consented patients from an ongoing audit of all patients admitted to or seen in outpatient Neurology clinic at (HKL). HKL is the main tertiary hospital in Malaysia that receives a high number of stroke patients and referred stroke patients from various areas from Klang Valley and throughout Malaysia; approximately 1000 to 1200 acute and recurrent stroke cases annually. The targeted patients are adults (age > 18 years) of adequate literacy, diagnosed with the first stroke past 6 months, no stroke before the index event and on stroke risk preventative medications. Those patients with a diagnosis of depression, cognitive impairment or with a stroke caused by accident will not be eligible for study participation. Furthermore, only those who can read, write, and speak English or Malay language are eligible to participate in this study.

### Sample size

2.3

A power analysis was carried out for an independent *t* test using the G∗Power version 3 to determine a sufficient sample size using an alpha of 0.05 and a power of 0.80.^[40]^ The estimation involved a medium effect size (*w* = 0.4) based on an average of effect sizes from similar recent studies associated to patient education in stroke, IMB, HBM, video narrative, and self-efficacy.^[25,41–43]^ However, sample size calculation according to stratification of stroke risk factors is not feasible because this is a disease with various underlying comorbidities and treatment heterogeneity. Thus, the desired sample size is 200 (100 each in intervention and control groups) are needed. With an estimated 15% attrition rate, 115 in each group will be recruited, thus yielding a target total sample size of 230.

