**Method::**

This is a behavioral randomized controlled trial of patient education intervention with video narratives for patients with stroke lacking medication understanding and use self-efficacy. The study will recruit up to 200 eligible stroke patients at the neurology tertiary outpatient clinic, whereby they will be requested to return for follow-up approximately 3 months once for up to 12 months. Consenting patients will be randomized to either standard patient education care or intervention with video narratives. The researchers will ensure control of potential confounding factors, as well as unbiased treatment review with prescribed medications only obtained onsite.

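### The abstract caps recruitment at 200, but section 2.3 needs 200 evaluable patients and recruits 230 to allow for attrition

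*Protocol article*

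**What the plan says.** The Method paragraph of the abstract sets a ceiling on recruitment: "The study will recruit up to 200 eligible stroke patients at the neurology tertiary outpatient clinic". These are the patients who then return about every 3 months for up to 12 months, so 200 is a number entering the trial, not a number completing it.

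Section 2.3 (Sample size) sets out the calculation. The test is named: "A power analysis was carried out for an independent *t* test using the G∗Power version 3". The error rates follow: "using an alpha of 0.05 and a power of 0.80". The effect size is given as 0.4 with the symbol *w*, described in these words: "The estimation involved a medium effect size". The requirement is that "the desired sample size is 200 (100 each in intervention and control groups) are needed". The section then turns this into a recruitment target: "With an estimated 15% attrition rate, 115 in each group will be recruited, thus yielding a target total sample size of 230".

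**The concern.** Both statements are current text and both are about recruiting. A maximum of 200 is incompatible with a target of 230. The 200 in the abstract matches section 2.3's requirement before the attrition allowance is added, so it appears to be the evaluable number carried over as a recruitment number.

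What is at stake is the stated power. If recruitment stops at the abstract's ceiling, the trial has no allowance for the loss that section 2.3 itself expects. Such loss is foreseen in section 3.1, where patients who miss visits, move away, are referred elsewhere, do not respond to reminders or have to be unblinded are withdrawn.

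Two smaller matters in section 2.3 should be tidied at the same time. The attrition allowance is computed by multiplying where it should divide. The effect-size symbol belongs to a chi-square test, although the calculation is for a t test.

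**Working it through.** **Inputs (section 2.3 unless noted)**
- Independent two-sample t test, equal arms, alpha 0.05, power 0.80
- Effect size 0.4, taken as Cohen's d
- Attrition 15%
- Recruitment: 230 (section 2.3) or at most 200 (abstract)
- Sidedness: not stated; two-sided is assumed and tested in step 1

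**1. Reproduce the plan's figure.** For n per arm, the exact power comes from the noncentral t distribution with noncentrality d × √(n/2) and 2n − 2 degrees of freedom. Solving for power 0.80 at d = 0.4:
- two-sided: n = 99.08, rounded up to **100 per arm, 200 in total**, as stated
- one-sided: n = 77.97, rounded up to 78 per arm
- reading 0.4 literally as the chi-square index *w* with 1 degree of freedom: N = 49.06, about 50 in total

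Of these, only the two-sided t test with d = 0.4 gives the plan's number.

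**2. Recruit 200, as in the abstract.** Evaluable per arm: 100 × (1 − 0.15) = 85. Noncentrality: 0.4 × √(85/2) = 2.608. Exact two-sided power: **73.7%**. The type II error rises from the planned 20% to about 26%, and the difference detectable with 80% power moves from 0.40 to 0.43.

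**3. Recruit 230, as in section 2.3.** Evaluable per arm: 115 × 0.85 = 97.75. Exact power: 79.2% at 97, **79.5%** at 97.75 and 79.6% at 98, against 80.4% at 100. The detectable difference at 97.75 per arm is 0.403. Against the exact need of 99.08, the shortfall is 99.08 − 97.75 = 1.33 patients per arm.

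**4. The inflation step.** The plan's 115 is 100 × 1.15. To keep 100 after losing a fraction 0.15 of those recruited, the sum is 100 / (1 − 0.15) = 117.6, so 118 per arm and 236 in total (118 × 0.85 = 100.3). Conversely, 115 per arm keeps 100 up to an attrition of 1 − 100/115 = 13.0%.

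| Recruited | Evaluable per arm at 15% loss | Two-sided power at d = 0.4 |
|---|---|---|
| 200 | 85 | 73.7% |
| 230 | 97.75 | 79.5% |
| 236 | 100.3 | 80.5% |

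**The case against.** **Section 2.3 governs.** It gives the recruitment target without ambiguity and shows where 200 comes from, while nothing in the body of the article supports a ceiling of 200. The 74% arises only if the abstract is followed. This stands as a reason to treat the matter as a text correction. It does not remove the contradiction.

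**The power loss assumes a t test on completers.** Section 4.3 also plans a mixed model over time and multiple imputation, and the primary measure is taken at five time points, so patients lost late still contribute. The trial also calls itself exploratory. So 74% is toward the pessimistic end of what a ceiling of 200 would give. However, section 2.3 chose to allow for attrition by recruiting more, and the abstract omits that allowance.

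**A reader might infer that 230 is underpowered too**, because 115 per arm does not leave 100 after 15% loss. The figures do not support that as a material point: the deficit is about 1.3 patients per arm and half a percentage point of power. The input of 0.4 is itself an average over several earlier studies, so its uncertainty is much larger than that.

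**A reader might also infer from the symbol *w* that the sample size is wrong by a factor of four**, about 50 against 200. The article does not support this either. It names the t test one sentence earlier, and the stated 100 per arm reproduces with d = 0.4. The symbol is a notation slip with no effect on the number.

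**Conclusion.** The contradiction between 200 and 230 is real and should be corrected. On the article's own 15% attrition, the abstract's ceiling gives 85 evaluable patients per arm and about 74% power, some 6 points below the stated 80%. The power figures rest on three assumptions: a two-sided test, 0.4 read as Cohen's d, and an analysis of completers only. The first two are supported by the fact that they reproduce the plan's 100 per arm. The conflict between the two targets depends on none of them.

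The inflation error and the effect-size symbol are minor. At 230 recruited, power is just under 80%, and no design decision turns on the difference. Severity: should-fix text correction.

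**What to change.** - **Abstract:** replace the ceiling of 200 with the section 2.3 target of 230.
- **Section 2.3, attrition:** keep 115 per arm and describe it correctly, either as allowing for 13% attrition or as leaving about 98 evaluable per arm at 15%, with power just under 80%. If the sponsor prefers to keep both 15% attrition and 100 evaluable per arm, the target is 118 per arm, 236 in total, and the abstract should then carry 236.
- **Section 2.3, effect size:** write Cohen's d = 0.4 in place of *w*, and state that the test is two-sided, if that is what was run.

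The cost is a few words in two places. No added patients are needed relative to section 2.3 unless the sponsor chooses full inflation, which adds six (236 − 230).

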### Randomization

2.4

Randomization will be performed by using blocks of varying lengths, between 2, 4, and 6 in opaque envelopes to avoid bias. The order of the blocks and the allocations within each block will also be randomized. Assigning of patients to one of two study arms will take place after the baseline screening.The standard care (control group); based on MTAC framework will receive an appropriate referral for rehabilitation, nutrition counseling, and speech therapy from the neurology department. Aside from treatment review and advice, the department also provides short message service (SMS) reminders of next appointments. Pamphlets regarding common patient education information about stroke, and its preventative treatment, as well as a self-monitoring calendar, will be distributed. The information developed according to HBM constructs and MTAC guidelines is about stroke symptoms, preventative treatment adherence advice, and medication management. The patients will be provided with a general helpline in case of any inquiry pertaining to their treatment.The intervention group, that will receive standard care procedures, printed materials, reminders, and helpline similar to those in the control group, will also obtain a short face-to-face video narrative of a doctor and a patient's reflection about stroke.

### The intervention

2.5

The video narrative and the video scripts have been developed from in-depth patient interviews, MTAC guidelines, HBM constructs, and stroke management guidelines. They have been designed to provide represented connected events and messages so as to motivate and to induce self-efficacy skills suited for the local context.^[15,29,44–46]^ An expert panel that consists of representatives from doctors, pharmacists, educationists, and stroke patients have employed a consensus on the video narrative and video scripts. Flesch-Kincaid reading level for the scripts, quotes, subtitles, and texts is an average grade level of six (6).^[47]^ In order to add value and to increase the impact of role model, a neurologist and a stroke patient were assigned to narrate the scripts so as to portray their true emotion and seriousness of stroke preventative measures. In addition, cues were highlighted in the video narrative as short quotes, while the subtitles were incorporated to increase comprehension of their messages.

## Data collection, management, and analysis

3

### Study procedures

3.1

With the supervision of a research neurologist, patient screening and randomization will be carried out by a clinic staff nurse who is not involved in this research. Patients will then complete their baseline assessments at the outpatient Neurology clinic. The neurologists will be blinded after the assignment. They will be advised to not to prompt patients regarding reception of intervention. One of the researcher ([name]) who is a pharmacist and a clinical educator, will conduct the baseline assessment. Patients randomized into the intervention arm will be displayed the video immediately after their clinic visit. All patients, regardless of study arm, will receive appropriate standard stroke treatment and medication management. At each consequent visit, the researcher will assess the level of medication understanding and use self-efficacy, while evaluation of stroke risk blood parameters will be done by the staff nurse at the clinic. The researcher will send reminder calls 3 days in advance to promote retention. At each clinic visit, both groups will receive MTAC standard care reminders to encourage self-monitoring, to modify lifestyle, to follow-up clinic appointments, and to enquire regarding their medications. Patients who miss their visits, move too far away, are referred to other outpatient clinics, and those who fail to respond up to 4 times of reminders will be noted as lost to follow-up and eventually withdrawn from the study. Also, if there is a need of unblinding due to the intervention's effect, the patient's allocation will be revealed to their neurologist and that patient is withdrawn from the study. These effects will be recorded and reported in the data analysis.

At each session, the patients will meet the neurologist first for their follow-up treatment review, and next, have further check on self-monitoring practice and lifestyle changes. The clinic staff nurse will assess their blood pressure and other appropriate blood parameters. After that, the clinic staff nurse will guide the patients into a quiet room, where the researcher will meet them individually for the outcome assessment or video viewing. The patients will view the video at baseline: T0, 3rd month: T1 and 6th month: T2 immediately after outcome measure assessment (Fig. 1).

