### Study design and aim

2.1

This is a single-blind, randomized controlled, parallel group, longitudinal, and exploratory trial in which patients with risk of recurrent stroke will receive either a video narrative and standard care or standard care alone. This study is due to start in the month of May 2018. The study outcomes are assessed as follows; at baseline: T0, 3 months: T1, 6 months: T2, 9 months: T3, and 12 months: T4, as outpatient follow-up. The design and the conduct of the study conform to the revised Consolidated Standards of Reporting (CONSORT) guidelines^[38]^ and adheres to Standard Protocol Items: Recommendations for Interventional Trials (SPIRIT)^[39]^ Approvals have been granted from the Malaysian Medical Research and Ethics Committee—MREC (NMRR ID-15-851-24737) and the Monash University Human Research Ethics Committee—MUHREC (ID 9640), while the study is registered with the Australian New Zealand Clinical Trials Registry—ANZCTR (ACTRN12618000174280) with Universal Trial Number (UTN) U1111-1201-3955. The research ethics committee and trial registry are notified if there are updates or protocol amendments. The study will be administered at the Neurology Department of Hospital Kuala Lumpur (HKL) in partnership with Jeffrey Cheah School of Medicine and Health Sciences, Monash University Malaysia.

The primary aim of the study is to determine if integrating a video narrative of a doctor and a patient into the standard patient education and counseling procedure will improve medication understanding and use self-efficacy, in comparison to the current standard patient education and counseling procedure. Here, the impact of reinforcement (e.g., repetition after 3 months’ interval at T1 and T2) will also be determined. Next, the secondary aim of this study is to explore the relationship between medication self-management and stroke risk factor control, as well as its effect on the quality of life among the stroke patients. The study achieves an endpoint if stroke recurs.

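### As written, patients are randomised before the T0 questionnaires, so baseline self-report scores could be influenced by knowledge of the arm

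*Protocol article*

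**What the plan says.** Section 3.1 (Study procedures) opens with the nurse's role: "patient screening and randomization will be carried out by a clinic staff nurse who is not involved in this research". The next sentence is: "Patients will then complete their baseline assessments at the outpatient Neurology clinic". Section 2.4 (Randomization) gives the timing as: "Assigning of patients to one of two study arms will take place after the baseline screening".

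The T0 assessor is one of the researchers, "who is a pharmacist and a clinical educator, will conduct the baseline assessment". At each session the nurse takes patients to a quiet room, "where the researcher will meet them individually for the outcome assessment or video viewing". On the order within the session, section 3.1 says: "The patients will view the video at baseline: T0, 3rd month: T1 and 6th month: T2 immediately after outcome measure assessment".

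On blinding, section 2.1 says: "This is a single-blind, randomized controlled, parallel group, longitudinal, and exploratory trial". Section 3.1 adds: "The neurologists will be blinded after the assignment". Section 4.3 says that the biostatistician and one other person, whose name is removed from the text, are blinded for the analysis.

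Section 4.1 lists MUSE at T0 and at every later visit, and the stroke knowledge test, BIPQ and BMQ-specific at T0, T2 and T4.

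**The concern.** Baseline values are useful in a randomised comparison because allocation cannot have affected them. That is guaranteed when they are recorded before the arm is known. If the envelope is opened first, it depends on the patient and the assessor both staying unaware until the questionnaires are complete.

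The exposed measures include a self-efficacy scale and scales of belief and illness perception. Answers to such scales can respond to expectation, for example in a patient who knows that a video will or will not follow, and to the manner of an assessor who knows the arm. A shift at T0 in one arm would enter any analysis that uses T0, and the analysis could not remove it because its size would be unknown. A lesser consequence is that a patient who leaves between randomisation and the questionnaires is randomised without a baseline.

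**Working it through.** **Order of events.** The two sections read together:

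| Source | What comes first | What comes next |
|---|---|---|
| Section 2.4 | baseline screening | assignment to an arm |
| Section 3.1, opening | screening and randomisation, by the nurse | baseline assessments, by the researcher |
| Section 3.1, end | outcome assessment at T0 | video, if allocated |

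Section 3.1 treats screening (nurse) and baseline assessment (researcher) as separate steps. With that usage the rows fit one sequence: screening, randomisation, T0 questionnaires, video. Section 2.4 does not contradict this, because it names screening and not assessment.

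**Who could know the arm at T0.** Blinding is stated for the neurologists and for the analysis staff. It is not stated for patients. Nor is it clearly stated for the researcher as assessor, since the removed name in section 4.3 leaves open whether that is the same person. Opaque envelopes conceal the allocation until assignment, not after it. No sentence says when the patient or the assessor learns the arm.

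**Which analyses use T0.** Section 4.3 plans a mixed model of group differences over time, in which T0 is one of the time points, and also t tests of mean differences. The article does not say whether the t tests use follow-up scores or changes.

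**Illustration of size.** The yardstick is the planned effect in section 2.3, 0.4, read as a standardised mean difference. With alpha 0.05 (taken as two-sided) and power 0.80, the t-test calculation gives 99.08 per group, rounded up to 100, which matches the article's figure.

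Let d be the shift at T0 in the intervention arm relative to control, in SD units, and r the correlation between T0 and follow-up scores. If the shift exists only at T0, the bias is:

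- follow-up score alone: 0
- change from baseline, or a group-by-time contrast against a freely estimated T0 mean: −d
- baseline-adjusted comparison: −r × d

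Neither d nor r is given in the article. Assume d = 0.1 to 0.2 and r = 0.5:

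- change from baseline: 0.1 to 0.2 SD; 0.1/0.4 = 25% and 0.2/0.4 = 50% of the planned effect
- baseline-adjusted: 0.5 × 0.1 = 0.05 to 0.5 × 0.2 = 0.10 SD; 0.05/0.4 = 12.5% and 0.10/0.4 = 25%

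The sign of d is unknown. A rise in MUSE in the intervention arm at T0 would hide benefit, and a fall would inflate it. The result also depends on the shift vanishing. If the same shift d persisted at follow-up, the change score would carry d − d = 0. The illustration is therefore one scenario and not an estimate.

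**The case against.** The strongest reply is that knowledge of allocation at T0 is nowhere documented. The nurse who randomises is outside the research team, a different person gives the questionnaires, and the arm might not be disclosed until the video is due. This stands. A reader might infer from the order alone that the T0 scores are contaminated, or that the treatment effect is biased by a quarter to a half of its planned size. The article supports neither inference. The first needs a fact that it does not give. The second needs an assumed shift that is present at T0 and absent afterwards, although the article has the researcher assess patients again at later visits, after intervention patients have seen the video.

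The video comes after the T0 assessment, so the intervention itself cannot reach the baseline scores. This also stands, and it leaves expectation and assessor behaviour as the only routes.

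The term used in section 2.4 might loosely cover the baseline questionnaires, and Figure 1, which section 3.1 cites, is not available here. That leaves some ambiguity. On the loose reading, however, sections 2.4 and 3.1 give opposite orders and need to be reconciled, so an edit is due either way.

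Loss between randomisation and the questionnaires is likely to be small if both fall within one visit, and multiple imputation is planned for missing data. That part of the concern carries little weight.

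**Conclusion.** The point holds as a weakness in the stated sequence. Read literally, sections 2.4 and 3.1 put allocation before the T0 questionnaires, and nothing in the article clearly keeps the patient or the assessing researcher unaware of the arm while they are completed. Influence on the T0 scores is possible but not shown, and neither its size nor its direction can be derived from the document.

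If it occurred, it would affect the mixed-model comparison over time and any change-based or baseline-adjusted comparison. A t test on follow-up scores alone would not be affected by it. The figures of 0.1 to 0.2 SD for a change score and 0.05 to 0.10 SD for an adjusted one rest entirely on the assumed shift, the assumed correlation of 0.5 and a shift confined to T0.

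This is worth correcting before enrolment because the change is cheap and the analysis could not undo the problem afterwards. It is not a defect that by itself undermines the trial.

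**What to change.** Amend sections 2.4 and 3.1 so that both give the same T0 sequence:

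1. consent and eligibility screening
2. all T0 questionnaires, blood pressure and blood samples completed
3. the envelope opened by the independent nurse
4. the video, if allocated

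In section 2.4, assignment should be said to follow completion of all baseline assessments. Figure 1 should be checked against the same order.

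The visit and the staff stay the same. The one practical cost is that the patient goes back to the nurse between the questionnaires and the video. That hand-back should be kept. Letting the researcher open the envelope would avoid it but would weaken the separation between the person who allocates and the person who assesses.

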### Statistical analysis

4.3

Data entry will be done independently by a clinic staff nurse and verified by another. Hardcopies of data collection forms and outcome measures will be kept in a locked safe, whereas softcopies are to be deposited at the repository center (Lab Archives), both at Monash University in Malaysia. Only the principal investigators ([name]), ([name]), and ([name]) have access to the interim results and makes the final decision to terminate the trial. The study team ensures that patients’ identity and personal information are coded to maintain confidentiality. In addition, ([name]) and the biostatistician ([name]), who will also be blinded, will conduct the statistical analysis by using International Business Machines Statistical Package for the Social Sciences (IBM SPSS; IBM Corp. Released 2013. IBM SPSS Statistics for Windows, Version 22.0. Armonk, NY) (v.22). The initial analysis will consist of descriptive statistics on demographic data, such as frequency distributions. Meanwhile the mean differences in primary and secondary outcomes are compared by using *t* tests or equivalent statistical method, whereas categorical outcomes are matched using chi square test. *P* values <.05 are considered statistically significant. Generalized mixed model analysis is adapted to investigate the variances between groups over time for all outcomes evaluated at the allocated time. Furthermore, the association between medication understanding and use self-efficacy, stroke knowledge, illness perception scores, as well as engagement in self-monitoring and clinic appointment attendance will be tested, as they seem to be critical indicators of behavioral changes. Multivariable analysis will be employed to examine the influence of the video narratives on stroke risk factor control and their covariates.^[61]^ Multiple imputation will be adapted to handle missing data if it occurs. In addition, withdrawn patients’ feedback about the intervention will be analyzed.

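### The researcher who runs the video sessions also assesses self-reported MUSE at every follow-up visit, so the primary outcome is assessed with knowledge of allocation

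*Protocol article*

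**What the plan says.** **Blinding.** Study design and aim states: "This is a single-blind, randomized controlled, parallel group, longitudinal, and exploratory trial". Study procedures says that the neurologists are blinded after assignment. The Statistical analysis section extends blinding to the analysis, referring to a person "who will also be blinded, will conduct the statistical analysis". No section says that whoever assesses outcomes is blinded.

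**Primary outcome assessment.** At T0 a study researcher "who is a pharmacist and a clinical educator, will conduct the baseline assessment". After that: "At each consequent visit, the researcher will assess the level of medication understanding and use self-efficacy". The Primary outcome measure section describes MUSE as a 0 to 32 scale of the patient's own confidence in understanding and using the prescribed medicines, taken at T0 to T4.

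**Video sessions.** After the clinic checks the nurse brings each patient to a quiet room, "where the researcher will meet them individually for the outcome assessment or video viewing". On timing: "The patients will view the video at baseline: T0, 3rd month: T1 and 6th month: T2 immediately after outcome measure assessment".

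**Nurses.** A clinic staff nurse described as outside the research does the screening and randomization. On the measurements: "The clinic staff nurse will assess their blood pressure and other appropriate blood parameters". On the data: "Data entry will be done independently by a clinic staff nurse and verified by another".

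**The concern.** MUSE records how confident patients say they feel. The video is meant to raise that confidence. If the person who collects the answers also ran the video sessions, two routes to bias open. The assessor may prompt, clarify or record differently according to arm. The patient may give the answer that this person seems to hope for. Either would most likely make the video look better than it is. A larger sample or multiple imputation removes neither.

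The single-blind label adds to the problem. A reader may take it to mean that outcome assessment is protected, when the blinded clinicians are not the people who assess MUSE.

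**Working it through.** **1. Who knows the allocation when MUSE is taken.** Reading the statements in Study procedures together:

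| Visit | Video shown that day | MUSE assessed by | Time since last video (video arm) | Does the assessor know the arm? |
|---|---|---|---|---|
| T0 | yes, after MUSE | researcher | none yet | not stated; randomization is described before the baseline assessment |
| T1 | yes, after MUSE | researcher | 3 months | yes, from the T0 session |
| T2 | yes, after MUSE | researcher | 3 months | yes |
| T3 | no | researcher | 3 months | yes |
| T4 | no | researcher | 6 months | yes |

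Control patients are known by exclusion, because they were seen at T0 without a video. All four post-baseline MUSE assessments are therefore made with knowledge of the arm.

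**2. The plan's own sample size.** Inputs from the Sample size section: effect size 0.4 (read as a standardised mean difference), alpha 0.05, power 0.80. Sidedness is not stated; two-sided is assumed.

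- Normal approximation: n per arm = 2(1.96 + 0.842)² / 0.4² = 98.1, rounded up to 99.
- Exact two-sample t test: 99.08, rounded up to 100 per arm, with power 0.804 at 100.
- A one-sided test would need 78 and does not match.

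The stated 100 per arm is reproduced, so 100 per arm and a two-sided t test are the right frame for the illustration.

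**3. What a spurious shift would do.** Suppose that there is no true effect and that unblinded assessment moves the arm difference in MUSE by b standard deviations. The t statistic then has noncentrality b × √(100/2) = 7.07b on 198 degrees of freedom. The chance of p < 0.05 is the probability that |t| exceeds 1.97.

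| Assumed shift b (SD) | Share of the planned 0.4 | Noncentrality | False-positive rate |
|---|---|---|---|
| 0 | 0 | 0 | 5% |
| 0.05 | one eighth | 0.35 | 6.4% |
| 0.10 | one quarter | 0.71 | 10.8% |
| 0.20 | one half | 1.41 | 29.1% |
| 0.30 | three quarters | 2.12 | 56% |

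The values of b are assumptions. The protocol gives neither a bias size nor a standard deviation for MUSE, so b cannot be turned into scale points.

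**The case against.** The best defence has several parts.

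- **The label is not false.** Study procedures says who is blinded and never claims a blinded MUSE assessor. That stands: this is a design weakness with an unclear label, not a broken promise.
- **The mode of administration is not given.** Patients may already fill in MUSE themselves, and a condensed article may leave this to the full protocol. That is fair, and it limits how strongly assessor influence can be asserted. It does not change the fact that the researcher meets each patient individually for the assessment and knows the arm.
- **Some demand is common to both arms.** The same researcher assesses everyone, and both arms get printed material, reminders and a helpline. Only the differential part biases the comparison. This is correct, and the shifts in the working stand for that part alone.

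Four stronger readings are tempting, but the text does not support them.

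- *A reader might infer that patients rate their confidence straight after the video.* The order is the reverse: each video follows that day's assessment, and later MUSE scores come 3 or 6 months after the last showing.
- *A reader might infer that the nurse who randomizes also measures blood pressure.* The role title is shared, but the data-entry sentence shows at least two such nurses. Only the lack of a stated separation can be noted.
- *A reader might infer that all outcomes are unprotected.* Under Secondary outcome measures, blood pressure is taken with a calibrated device and blood samples go to the hospital laboratory. These are much less open to influence than a confidence rating.
- *A reader might infer that a blinded analyst is the researcher who shows the video.* Names are removed, so this cannot be settled either way.

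**Conclusion.** The point holds for the primary outcome. The researcher who runs the video sessions also assesses self-reported MUSE at T1 to T4, and so knows the allocation at each of those visits. The blinding of the neurologists does not protect MUSE, and patients cannot be blinded to having seen a video. The bias would probably favour the video arm.

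Its size is unknown. At assumed shifts of 0.1 and 0.2 SD with 100 per arm, the false-positive rate would be about 11% and 29% instead of 5%. This rests on a two-sided t test, no true effect and all of the shift being differential between arms. It also reads the researcher at follow-up as the one who runs the video sessions, as Study procedures does in its wording.

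The trial remains feasible as designed. The change is worth making because the threat is foreseeable, bears on the main result and can be reduced with little effort.

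**What to change.** 1. **Collection.** Patients complete MUSE and the other questionnaires themselves in the quiet room and seal them before meeting the researcher at that visit. The researcher may then show the video as planned. Ability to read and write English or Malay is already an entry criterion. Where a patient with a disability needs help, use a standard script and record that help was given.
2. **Video delivery.** Leave this with the researcher. Passing it to the nurse who escorts patients could reveal the arm to a person who measures blood pressure.
3. **Analysis.** Run it on masked arm codes, by someone who did not deliver the video.
4. **Label.** State the blinding as: *treating neurologists and analysts blinded; patients and the researcher delivering the video not blinded.*
5. **Nurse roles.** State that the nurse who opens the envelopes is not the one who measures blood pressure for those patients.

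**Cost.** Changes of wording and of the order of steps within a visit, with existing staff. There may be more blank items, and some patients will need scripted help. Sealed self-completion reduces influence from the assessor but does not remove patients' own expectation, so the report should state that as a limitation.
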